#### Exploration of influencing factors

2.4.5

Differences in the characteristics of respondents in different categories of demand patterns will be analysed using the Kruskal–Wallis rank tests (for ordinal measurements), one-way analysis of variance (for interval measurements), or chi-square tests (for nominal measurements). We will also perform a polynomial regression analysis to determine the factors that influenced the categories of needs of older adults, primarily by dividing the potential classes of rehabilitation of older adults obtained by LCA into dependent variables. According to the theoretical framework, relevant covariates will be included to analyse the influencing factors of the older adults’ CBR needs. The influencing factors in the theoretical framework will determine the dimensions of the collection of covariates. The covariates and their allocations are listed in Table 3.

**Table 3 tab3:** Covariates included in the analysis of influencing factors of older adults’ community-based rehabilitation needs.

Covariate	Definition/Measuring tools	Variable type	Units/categories

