#### Sampling

2.3.3

LCA model building requires numerous parameters, resulting in a sample size that depends on the necessary model analysis. Therefore, standard sample size calculations cannot comply with LCA requirements. For LCA, some researchers have suggested a minimum sample size of 500 (49), whereas others recommend a minimum sample size ranging from 300 to 1,000 (50, 51); therefore, we plan to recruit at least 4,000 participants. The sample size will satisfy the analytical requirements.

A probability-proportionate-to-size (PPS) sampling method will be used to select participants from Guizhou Province. PPS sampling requires the number of clusters to be not less than 30. In this study, we will assume the selection of 50 groups, with 4,000 people categorised into 50 groups, each containing 80 participants. These 50 groups will be drawn from six county-level cities and three autonomous prefectures. The number of clusters (*n*) in each of six county-level cities and three autonomous prefectures will be calculated as follows: ① The population aged ≥60 years in Guizhou Province (*N*) divided by 50 and ② The number of clusters (*n*) will be equal to the number of integer multiples of n/50 in the corresponding city cumulative population interval. Then, *n* natural villages/streets in the corresponding prefecture-level cities will be randomly selected as *n* clusters relative to the cities. Detailed information on each prefecture-level city cluster is presented in Table 2.

**Table 2 tab2:** Clusters in six county-level cities and three autonomous prefectures.

Township	Population	Accumulative population	*n* of clusters
1.Guiyang	795,475	795,475	7
2.Zunyi	1,126,525	1,922,000	9
3.Liupanshui	409,888	2,331,888	3
4.Anshun	392,951	2,724,839	3
5.Bijie	954,763	3,679,602	8
6.Tongren	579,146	4,258,748	5
7.Qiandongnan	642,509	4,901,257	5
8.Qiannan	585,724	5,486,981	5
9.Qianxinan	443,626	5,930,607	4
Total	*N*	5,930,607	50

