#### Evaluation and classification

2.4.3

Evaluation indicators commonly used in LCA models will be used to evaluate our models, such as the Akaike Information Criterion, Bayesian Information Criterion (BIC), and sample-size-adjusted box BIC (aBIC). It is believed that the accuracy of using BIC for evaluation is higher when the sample size is large; therefore, we have chosen BIC for the evaluation of this index (52). The smaller the value, the better the fitting degree of the model. Classification accuracy will be evaluated using entropy, which ranges from 0 to 1; the closer the value is to 1, the more accurate the classification (54). Finally, the Lo–Mendel–Rubin and bootstrap-based likelihood ratio tests will be used to evaluate the fitting differences of the LCA models. Statistical significance is set at *p* < 0.05.

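### The survey samples clusters of 80 people per village or street, but the named group tests assume independent respondents and no allowance for clustering is stated, which matters most for covariates fixed by place

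*Protocol article*

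**What the plan says.** Section 2.3.3 (Sampling) sets out a cluster sample. The number of clusters per area is allotted in proportion to the population aged 60 or over, and then "natural villages/streets in the corresponding prefecture-level cities will be randomly selected as" the clusters. The size is given as "with 4,000 people categorised into 50 groups, each containing 80 participants".

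Section 2.4.4 assigns each respondent to the most probable class and reports the share of people in each class. Section 2.4.5 (Exploration of influencing factors) compares the classes: "Differences in the characteristics of respondents in different categories of demand patterns will be analysed using" Kruskal–Wallis tests for ordinal variables, one-way ANOVA for interval variables and chi-square tests for nominal variables. A regression of class membership on the Table 3 covariates follows. It is called polynomial and is apparently multinomial. Significance is set at p < 0.05 (sections 2.3.6 and 2.4.3).

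Sections 2.3.6 and 2.4 to 2.4.5 mention no clustering, robust or design-based variance, or multilevel model.

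**The concern.** People in one village or street share facilities, distances, services and surroundings, so their needs are likely to be more alike than those of people drawn at random from the province. A test that counts 80 such respondents as 80 independent observations understates the sampling error.

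The effect is largest for covariates that take nearly the same value across a cluster. Table 3 has four candidates: community rehabilitation facilities, distance to the nearest institution, barrier-free environment and type of community (city, fringe or countryside). For these the information comes mainly from about 50 places and not from 4,000 people.

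Research question (iii) in section 1.3 asks which factors are associated with need, and contextual characteristics are one of the four dimensions of the framework. A false positive would therefore fall on one of the study's stated aims. The class shares in section 2.4.4 would also look more precise than they are.

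**Working it through.** **Inputs from the article.** 50 clusters and 80 people per cluster (section 2.3.3); significance level 0.05, taken as two-sided because the side is not stated. **Assumed:** the ICC, for which the article gives no value; 0.01 to 0.10 is used as a range.

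**The plan's own figure.** 50 × 80 = 4,000, which reproduces. The cluster counts in Table 2, however, add to 7 + 9 + 3 + 3 + 8 + 5 + 5 + 5 + 4 = 49, against a stated total of 50. With 49 clusters the sample would be 49 × 80 = 3,920.

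**Class proportions, and covariates constant within a cluster.**
- Design effect: DEFF = 1 + (80 − 1) × ICC
- Standard error too small by a factor of √DEFF
- Effective n = 4,000 / DEFF
- Actual error rate of a nominal 5% test on one degree of freedom (covariates only) = 2 × [1 − Φ(1.96 / √DEFF)]

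| Assumed ICC | DEFF | SE factor | Effective n | Actual error rate |
|---|---|---|---|---|
| 0.01 | 1.79 | 1.34 | 2,235 | 14% |
| 0.02 | 2.58 | 1.61 | 1,550 | 22% |
| 0.05 | 4.95 | 2.22 | 808 | 38% |
| 0.10 | 8.90 | 2.98 | 449 | 51% |

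**More than two classes.** A chi-square test of a two-category covariate across three classes has 2 degrees of freedom and a critical value of 5.991. If the same DEFF applies to every contrast, the rejection rate is exp[−5.991 / (2 × DEFF)], which gives 19%, 31%, 55% and 71% for the four rows. The one-degree-of-freedom figures are therefore not the worst case.

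**Covariates that vary within clusters.** Here DEFF is approximately 1 + 79 × ICC(need) × ICC(covariate). With ICC(covariate) assumed to be 0.05:
- ICC(need) 0.02: DEFF 1.08, actual error rate 5.9%
- ICC(need) 0.05: DEFF 1.20, actual error rate 7.3%
- ICC(need) 0.10: DEFF 1.40, actual error rate 9.7%

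With ICC(covariate) at 0.10, the same three values of ICC(need) give 6.9%, 9.7% and 14.3%. The size of the problem thus depends on how strongly each covariate follows place.

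**Does clustering undermine the sample size?** Effective n falls below 1,000 at ICC = 3/79 = 0.038, below 500 at 7/79 = 0.089, and below 300 at about 0.156.

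**The case against.** The strongest reply is that this is a condensed article and that variance options are commonly left to an analysis plan. That stands for the LCA and the regression. The article is silent on how their standard errors are obtained, and a reader should not infer that it declares 4,000 independent respondents there. It does not rescue the group comparisons, because section 2.4.5 names specific tests that, as named, do not fit the article's own sampling.

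Second, most of the 25 covariates in Table 3 are personal, such as gender, age, marital status, chronic disease and frailty. Even the place-related ones are collected by individual questionnaire, so neighbours may disagree on whether facilities are adequate or access is barrier-free. This also stands. It means that the larger error rates are an upper case for self-reported context items and do not describe the analysis as a whole. The article names no confidence intervals either.

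Third, two stronger readings are tempting and unsupported:
- *The class-number tests will favour extra classes.* Section 2.4.3 says that Lo–Mendell–Rubin and "bootstrap-based likelihood ratio tests will be used to evaluate the fitting differences of the LCA models". If villages differ only in the mix of classes, the pooled data still follow the same class model and no extra class is needed. Spurious classes would require item responses within a class to differ by village. The article gives no ground to assume that, and the design effect does not measure it.
- *The sample is too small.* Section 2.3.3 states "The sample size will satisfy the analytical requirements", against cited minimums of 500 or 300 to 1,000. That statement survives most of the assumed ICC range. Effective n for a proportion is also not the quantity that such rules of thumb address.

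**Conclusion.** The point holds in limited form. The design is clustered, the three named tests assume independence in their standard form, and no adjustment is stated for the comparisons, the regression or the class proportions.

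The consequence is material for class proportions and for the covariates that are largely fixed by place, and slight for person-level covariates that cluster weakly. The figures rest on assumed ICCs, on equal clusters of 80, and on a design effect that ignores any gain from stratifying by area. A pilot or literature ICC would place the study within the range. Even the lowest value used, 0.01, nearly triples the error rate for a covariate constant within a cluster.

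No conclusion follows about the number of classes that will be chosen or about the adequacy of 4,000 respondents for fitting the LCA.

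**What to change.** 1. State that the village/street identifier stays in the analysis data set, in coded form. The de-identification step in section 2.3.4.2 should not remove it.
2. Fit the LCA and the class regression with cluster-adjusted variance, either design-based or multilevel, with the nine areas as strata. Report class proportions with those standard errors.
3. In section 2.4.5, replace the Kruskal–Wallis, ANOVA and chi-square tests with design-based Wald or Rao–Scott versions. Use degrees of freedom equal to clusters minus strata: 50 − 9 = 41, or 49 − 9 = 40 if the Table 2 counts are right. Reconcile Table 2 with the stated 50.
4. As a check only, repeat the class-number tests in a cluster-robust form or by resampling whole clusters.

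No extra data are needed if the identifier is recorded at collection. The cost is wider standard errors, some loss of power for context factors and slightly more analysis work.

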**Individual characteristics**			
Gender	Older adult’s gender	Categorical	1 = Male, 2 = Female
Age	Older adult’s age	Continuous	Years (roughly divided into 3–4 categories)
Ethnicity	Older adult’s ethnicity	Categorical	1 = Han ethnicity 2 = Other ethnicity
Education level	Current highest level of education	Categorical	1 = Primary education or below 2 = Junior high school 3 = Senior high school 4 = University or college above
Marital status	Current marital status	Categorical	1 = Married 2 = Divorced 3 = Widowed 4 = Never married
Number of children	Number of living children	Categorical	1 = 1 2 = 2 3 = ≥3
Employment status	Employed status in the past year	Categorical	1 = Formal work 2 = Informal work 3 = Retirement
Living resident	Current residence of older adults	Categorical	1 = City community 2 = Urban–rural fringe community 3 = Countryside community
Income groups	Personal income in the past year	Categorical	1 = Low income 2 = Lower middle income 3 = Middle income 4 = Upper middle income 5 = High income
Source of income	Source of the primary income	Categorical	1 = Pension 2 = Work income 3 = Relatives support 4 = Salary 5 = Other
Medical insurance	Medical insurance types	Categorical	1 = Basic Medical Insurance 2 = Commercial Medical Insurance 3 = No Medical Insurance
Having chronic disease	Suffering from chronic diseases	Categorical	1 = Yes 2 = No
Number of chronic diseases	Number of existing chronic diseases	Categorical	1 = 1 kind 2 = 2 or more
Types of chronic diseases	Classification of chronic diseases	Categorical	1 = Respiratory diseases 2 = Cardiovascular diseases 3 = Cerebrovascular diseases 4 = Digestive system diseases 5 = Metabolic diseases 6 = Other

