#### Quality control

2.3.5

Before the formal investigation, we will train the community and street staff to unify the standards and investigation methods to ensure that the investigation data are objective and accurate.To ensure that the survey results are true and accurate for items that older people do not understand during the filling process, we will use a unified language to explain them.The questionnaire star will be set up to ensure that each option is filled in to ensure the completeness of the content and efficiency of the recovery.The obtained data will be double-checked; if there is any difference, the data will be checked with the original data and corrected to ensure accuracy.

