**Context characteristics**			
Community rehabilitation facilities	The community’s facilities fulfil essential rehabilitation requirements.	Categorical	1 = Satisfy, 2 = Not satisfy
Distance to rehabilitation institution	Distance to the nearest rehabilitation institution	Categorical	1 = Suitable (<2 km) 2 = Relatively far (2–4 km) 3 = Very far (>4 km)
Awareness of rehabilitation services	Knowledge of rehabilitation services provided in the community	Categorical	1 = Yes, 2 = No
Rehabilitation service fee	Evaluation of rehabilitation service fee standard	Categorical	1 = Very low 2 = Relatively low 3 = General 4 = Relatively high 5 = Very high
Barrier-free environment	The environment is designed to be accessible and accommodating to needs	Categorical	1 = Yes, 2 = No

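### Table 3: the employment, insurance, service-fee and income codes are not mutually exclusive and exhaustive, while the form requires every item to be answered

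*Protocol article*

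**What the plan says.** Section 2.4.5 presents Table 3 as the list of covariates and their codes for the regression of latent class on respondent characteristics. Each row has one code list. Four rows matter here:

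- Source of primary income: "1 = Pension 2 = Work income 3 = Relatives support 4 = Salary 5 = Other".
- Employment status over the past year: "1 = Formal work 2 = Informal work 3 = Retirement".
- Medical insurance: "1 = Basic Medical Insurance 2 = Commercial Medical Insurance 3 = No Medical Insurance".
- Service fee, defined as "Evaluation of rehabilitation service fee standard": five levels from very low to very high. The row above it, awareness of community rehabilitation services, may be answered No.

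On completeness, section 2.3.5 (Quality control) states: "The questionnaire star will be set up to ensure that each option is filled in". Section 2.3.4.2 (Data management) adds that the electronic form will limit missing values. The article describes no skip rule, multiple-response format or not-applicable code.

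Eligibility (section 2.2.2, carried into the main study by 2.3.2) covers community-dwelling people aged 60 or over. It sets no condition on work history, insurance, or awareness or use of rehabilitation.

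**The concern.** A categorical covariate supports a clean contrast only if every eligible person fits exactly one code. In three of these rows some eligible people fit no code or two, and in the income row two codes overlap. With an answer required, such a person or the helping researcher must choose a code that is not true. The affected coefficients are then blurred or biased. A fee rating from someone who does not know the services is not a measurement of perceived cost. What is at stake is research question (iii), the factors associated with need patterns.

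**Working it through.** There is no stated figure to dispute, so the check sets each code list against the people the protocol admits.

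| Row | Person admitted | Valid codes | Recoverable after the survey? |
|---|---|---|---|
| Employment | Homemaker, never employed, unemployed | 0 | No |
| Insurance | Holds basic and commercial cover | 2 | No |
| Service fee | Unaware of the services, no view on fees | 0 | No: a forced rating cannot be told from a real one |
| Source of income | Wage earner | 2 (codes 2 and 4) | Yes: merge 2 and 4 |

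Income has an *Other* code, so that row is exhaustive and its only defect is overlap.

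**Can the four rows be sized?** No. Insurance shows why. Let d be the share with both covers, c the share with commercial cover only, and s the fraction of dual holders coded *Basic*. The fraction of commercial-cover holders coded *Basic* is s × d / (d + c). Assuming d = 10%, c = 1% and s = 0.5 gives 5/11 = 45%, which is 5% of all respondents, or 0.05 × 4,000 = 200 people. None of these inputs is in the documents. With s = 0.5 the fraction can lie anywhere from 0 to 50% depending on d and c; with s free, from 0 to 100%.

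**Other rows with the same fault.** Number of children is coded "Number of living children Categorical 1 = 1 2 = 2 3 = ≥3", with no zero, although marital status includes never married ("1 = Married 2 = Divorced 3 = Widowed 4 = Never married"). Chronic disease may be absent ("Suffering from chronic diseases Categorical 1 = Yes 2 = No"), yet number of diseases starts at one and type of disease has no none code. Satisfaction has no code for people who have not used the services, although treatment in the past year may be No.

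Only the chronic-disease rows can be sized from the article. Inputs: N = 50 × 80 = 4,000 (section 2.3.3); prevalence of any chronic disease 69.13% and of multiple diseases 45.5% (section 1.1), assumed to apply in Guizhou.

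- No chronic disease: 4,000 × (1 − 0.6913) = 1,234.8, about 1,235 people with no valid code for number or type.
- If all were forced into the one-disease code and 45.5% refers to all older adults, the true single-disease share is 0.6913 − 0.455 = 0.2363. The wrong fraction of that code is 0.3087 / (0.3087 + 0.2363) = 57%.
- If 45.5% refers only to people with a disease, the single-disease share is 0.6913 × (1 − 0.455) = 0.3768 and the wrong fraction is 0.3087 / (0.3087 + 0.3768) = 45%.
- If they were skipped instead, a complete-case regression keeps about 4,000 × 0.6913 = 2,765 people, among whom having a chronic disease is constant and drops out (design rank 2 of 3 columns).

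These figures belong to the chronic-disease rows and do not size the four rows above. For children the childless share is not given; an assumed 1% to 5% would be 40 to 200 people.

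**The case against.** Table 3 is analysis coding, not the questionnaire screen. The form is not shown, and an article may leave response formats to a fuller document. Skip rules or multi-select items may exist. This stands: single-choice format and forced miscoding are inferences. It does not remove the point, because Table 3 states the levels that will enter the regression, and it has none for these respondents however the form is built.

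Trained researchers will be present and will explain items in standard wording, so an arbitrary choice between codes is a worst case. That also stands, but an explanation cannot supply a code that is missing.

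Salary and work income may be meant as formal and informal earnings, matching the employment row. That is plausible, but the table does not say so. A reader might infer that the income overlap does lasting damage. It does not: merging codes 2 and 4 loses no defined information, and section 2.3.6 already plans data conversion.

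The fee item is not worded as limited to community services, so someone unaware of local provision may still hold a view. This weakens the example without answering it, since a person with no view still has no level; the middle code is a rating, not a do-not-know.

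**Conclusion.** The point holds as a coding defect in four of the 25 covariates in Table 3, with the same fault in the children, chronic-disease and satisfaction rows. Employment, insurance and fee need attention before the survey because the missing information will not have been collected; income can be corrected at any time.

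A reader might infer that the latent classes are compromised. They are not: these covariates are not the need items on which the classes are built, and research questions (i) and (ii) are answered from the latent class model. A reader might also want a misclassification rate for the four rows. The documents give no share for any of them, and the 45% insurance figure only illustrates its assumptions. Whether the practical result is wrong codes or structural missing data depends on the unseen form. It is worth correcting because correction is nearly free, not because a large bias has been shown.

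**What to change.** Before Phase 3:

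- Employment: add a code for not working and not retired.
- Insurance: record basic and commercial cover as two yes/no items, or add a code for both.
- Service fee: add a do-not-know / not-aware level and model it as its own level.
- Income: merge *Work income* and *Salary*, or define them apart.
- Other rows: add a zero code for children and for number of chronic diseases, record each disease type as yes/no, and add a not-used level for satisfaction. Once number of diseases has a zero code, it fully determines whether a person has a chronic disease (design rank 3 of 4 columns), so enter only one of the two.

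State in Table 3 or section 2.3.5 which items are skipped or multiple-response. The cost is edits to the electronic form and a few extra dummy variables; the Phase 2 pilot is a natural place to try the revised lists.

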### Background

1.1

Population ageing is accelerating worldwide, and this demographic transition presents a formidable challenge in managing global public health policies. In China, the estimated older population is expected to increase from 267 million in 2021 to 400 million in 2035, constituting 30% of the total population (1). As people age, their functional performance and intrinsic abilities decline (2), leading to an increased occurrence of chronic illnesses, geriatric syndromes, and multiple medical and psychosocial conditions (3). Studies in China have indicated that the prevalence of chronic diseases in older adults is 69.13% (4), with multiple chronic diseases, pain, mobility disorders, and depressive disorders occurring in 45.5% (5), 30% (6), 19.6% (7), and 36.8% (8) of older adults, respectively, which can profoundly influence their health status and quality of life (9). These findings indicate the importance of offering rehabilitation services to older adults to support their physical, psychological, and social wellbeing.

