**Outcome**			
Health status	Self-assessment of health status	Categorical	1 = Poor 2 = Moderate 3 = Good
Satisfaction	Rehabilitation service satisfaction	Categorical	1 = Very dissatisfied 2 = Not very satisfied 3 = Average 4 = Relatively satisfied 5 = Very satisfied
Self-care ability	ADL scale measurement	Categorical	1 = Complete self-care 2 = Decreased self-care ability 3 = Self-care disability
Frail	TFI scale measurement	Categorical	1 = Yes, 2 = No

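### Four covariates in Table 3 lack a none or not-applicable level, and the three chronic-disease rows cannot be used together in the regression for question (iii)

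*Protocol article*

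**What the plan says.** Section 2.4.5 states that Table 3 gives the covariates and their coding for the analysis of influencing factors, which serves research question (iii). Under individual characteristics the table has three chronic-disease rows:

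- *Having chronic disease*: yes or no.
- *Number of chronic diseases*: "1 = 1 kind 2 = 2 or more".
- *Types of chronic diseases*: one categorical variable with six codes, beginning "1 = Respiratory diseases 2 = Cardiovascular diseases 3 = Cerebrovascular diseases" and ending with 'other'.

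*Number of children* counts living children as 1, 2, or 3 and above. Under the outcome block, *Satisfaction* is defined as "Rehabilitation service satisfaction" and has five levels, from very dissatisfied to very satisfied. Two health-behaviour rows, on seeking services and on rehabilitation treatment in the past year, are yes/no.

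Sections 2.2.2 and 2.3.2 admit the general community-dwelling population aged 60 and over. Disease, children or service use are not required. On completeness, Section 2.3.5 says: "The questionnaire star will be set up to ensure that each option is filled in".

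**The concern.** A covariate coding should give every eligible person exactly one correct value. Four rows do not. A person without chronic disease has no correct number or type. A person with, say, a respiratory and a metabolic disease has two correct types and one place to put them. A person with no living children has no correct code, although the same table has a never-married level. A person who has never used a rehabilitation service has nothing to rate.

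The regression for question (iii) is at stake. Disease-free people are the natural reference group for any morbidity effect, and they are the ones whom the coding leaves out. If the form does force an entry, a childless person recorded as having one child, or a multimorbid person recorded under one type, cannot be put right after collection.

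**Working it through.** **Inputs**

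- Sample: "we plan to recruit at least 4,000 participants" (Section 2.3.3), made up as "4,000 people categorised into 50 groups, each containing 80 participants". Check: 50 × 80 = 4,000, which reproduces the stated size.
- Any chronic disease: "the prevalence of chronic diseases in older adults is 69.13" per cent (Section 1.1).
- Multiple chronic diseases: 45.5% (Section 1.1, from a different cited source).
- Childlessness and service non-use: no rate is given.

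**Can the three disease rows enter one model?** Take a respondent who answers 'no' to having a chronic disease. There are three ways to treat the number and type rows.

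1. *An entry is forced.* The respondent receives a number of at least 1 and a type, both false and both in conflict with the 'no'.
2. *The rows are skipped and left blank.* A complete-case regression containing all three rows keeps only people who answered 'yes'. *Having chronic disease* is then constant, and its effect cannot be estimated.
3. *The rows are recoded to 0 or none.* The indicators for '1' and '2 or more' now sum exactly to the indicator for *Having chronic disease*, which becomes redundant. A none level in the single type variable does the same.

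This holds at any prevalence below 100%.

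**How many people are concerned, if the background rates applied to the sample?**

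- No valid number or type code: (1 − 0.6913) × 4,000 = 0.3087 × 4,000 = 1,235 (30.9%).
- Left in a complete-case model because of the disease rows alone: 0.6913 × 4,000 = 2,765.
- Two or more diseases: 0.455 × 4,000 = 1,820. This is an upper bound on those who need more than one type code, because two diseases can fall in the same group.

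**The other two rows, over assumed ranges.** These figures assume independence and complete-case analysis with the items left blank; the rates are assumptions, not taken from the protocol.

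- Children: loss = 1 − 0.6913 × (1 − c), where c is the childless share. For c = 2%, 5% and 10% the loss is 32.3%, 34.3% and 37.8%.
- Satisfaction in the same model as the disease rows: number kept = 0.6913 × u × 4,000, where u is the share of service users. For u = 70%, 50%, 30% and 10% this leaves 1,936, 1,383, 830 and 277.

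**The case against.** The strongest reply is that Table 3 lists analysis covariates and is not the form itself. Section 2.2.3.1 names having a disease alongside its type and number, which suits a gate question with follow-ups. Skip logic and multiple selection are details that an article may leave out, and mandatory fields can coexist with skip rules. Section 2.3.6 provides for data conversion, so a 0 / 1 / 2-or-more count could be derived from two of the rows. Section 2.4.5 does not say that every row enters one joint model, and no missing-data method is named.

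Much of this stands, and it rules out several stronger readings:

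- A reader might infer that Table 3 cannot record people without disease or treatment at all. It can, through the yes/no rows; the gap is in the dependent rows.
- A reader might infer that false answers, or the loss of a third of the sample, are certain. Both depend on form logic and complete-case handling that the article does not state. The 30.9% comes from the disease rows alone and from a background figure that is not presented as a Guizhou estimate.
- A reader might subtract 45.5% from 69.13% and conclude that only 945 people surely have one valid type. That mixes two sources.
- A reader might call the result biased in every case. Dropping disease-free people restricts the population; it does not by itself bias the coefficients among those who remain.

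What the reply does not do is repair the stated coding. Skip logic prevents false answers but leads to the second or third treatment in the working. Separate models would avoid that conflict, but the number and type models would still leave out disease-free people. Multiple selection yields answers that one six-level variable cannot hold. Childlessness cannot be recovered from any other row, since marital status does not determine it. The past-year treatment row does not identify people who have never used a service.

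**Conclusion.** The point holds as a fault in the stated coding. Number of diseases, disease type, number of children and satisfaction are not exhaustive for the eligible population. Type is also not suited to people whose conditions fall in several groups, and the three disease rows cannot be used together as listed.

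The size is conditional. If the 69.13% prevalence held in the sample, about 31% (1,235 of 4,000) would have no valid number or type code. If the 45.5% held, up to 1,820 might need more than one type code. Childlessness and service non-use would add to this by an amount that the protocol cannot supply.

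The effect is confined to the analysis of influencing factors for question (iii). The latent class analysis uses the needs questionnaire items and is not touched.

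**What to change.** Revise Table 3 and the electronic form before the form is locked:

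- Replace *Having chronic disease* and *Number of chronic diseases* with one variable coded 0 / 1 / 2 or more.
- Record disease type as six yes/no indicators, so that several can apply and 'none' is all six at no.
- Add 0 to *Number of children*.
- Add a never-used level to *Satisfaction*, or analyse satisfaction among users only, in a separate model.
- State skip rules for inapplicable items, so that mandatory completion applies only to items that concern the respondent.

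The cost is a few more response options and skip rules, a revised table, and a few more model parameters, which a planned sample of 4,000 should readily carry. A users-only satisfaction model would rest on a smaller sample, and its results would apply to users only.
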